# LIST OF ABBREVIATIONS

| **Behvr** | Behavior |
| --- | --- |
| **BREATHE** | Behavioral Research of Environment and Air Pollution Through Education |
| **HIPAA** | Health Insurance Portability and Accountability Act of 1996 |
| **ICF** | Informed consent form |
| **IRB** | Institutional Review Board |
| **KIPP** | Knowledge Is Power Program |
| **MID** | Minimally important difference |
| **RCT** | Randomized controlled trial |
| **SFVAMC** | San Francisco Veterans Affairs Health Care System |
| **UCSF** | University of California San Francisco |
| **Ustdg** | Understanding |

# PROTOCOL SYNOPSIS

| **Title** | Behavioral Research of Environment and Air pollution Through Education (BREATHE) Study |
| --- | --- |
| **Number of sites** | This is a single-center study involving two UCSF-affiliated sites and two community-based sites. |
| **Rationale** | Air pollution is a major environmental problem with important health consequences including cancer, cardiovascular, and pulmonary diseases that affects billions of people around the world. Multiple studies have shown air pollution in general and its individual components, such as ozone and particulate matter, to be associated with increased morbidity and mortality in humans. Despite the wealth of scientific literature on the health effects of air pollution, the public’s personal choices in their daily lives continues to be largely detrimental towards the environment, and the public support for generation of policies to regulate sources of pollution has remained modest at best. One potential cause of the disconnect between the state of scientific knowledge and the public and political support for aggressive regulation to protect the environment may be the lack of awareness and understanding of the available knowledge. However, there has been substantial media attention to the ongoing environmental problems in the recent years and, despite this publicity, the public and political support for the necessary steps to battle air pollution has remained low. An important impedance to the required support for environmental protection may be the established lifestyle demands of the current generations of adults. The current adult generations have mostly grown with little understanding of the human contribution to air pollution and their impact on the environment, making any substantial change to their behavior challenging.  A potential solution to this problem may be to focus on the future generations to see whether providing appropriate education may result in lifestyles that include beneficial behaviors towards the environment since their lifestyles and habits are as yet unformed and more amenable to influence. However, whether teaching the adolescents about the health effects of air pollution would affect their future understanding and awareness of air pollution or forms their future behavior to more environmentally sound life choices is unclear. |
| **Study design** | This is a randomized control clinical trial of efficacy of a one-hour teaching session on air pollution on the understanding and behavioral choices of adolescents. |
| **Primary objective** | The primary objective of this study is to determine whether a short interactive evidence-based teaching session on air pollution could shift the behavioral choices of adolescents towards environmentally friendlier options. |
| **Secondary objectives** | A secondary objective of the study is to determine short interactive evidence-based teaching session on air pollution improves understanding and awareness of air pollution in adolescents. |
| **Number of subjects** | 600 |
| **Subject selection criteria** | Inclusion Criteria:   1. 13-15 years of age. 2. Middle school student. 3. Ability to read, understand, and write in English (at the middle-school level). 4. Willingness to participate in follow-up visits of the study.   Exclusion criteria:   1. Learning disabilities such as autism. 2. Moving out of the area within the next 6 months. 3. Inability to complete pre-intervention questionnaire. |
| **Test product, dose, and route of administration** | One hour teaching session on air pollution, one time. |
| **Control product, dose, and route of administration** | One hour teaching session on vaccination, one time. |
| **Duration of subject participation and duration of study** | Completion of all study procedures will require an active time commitment of two and half **hours** over a period of twelve months. The breakdown of time commitment per In-Person Visit is mentioned below:   - Visit 1: 105 minutes   - Pre-teaching survey   - Teaching session including spirometry   - Post-teaching survey - Visit 2: 15 minutes. - Visit 3: 15 minutes. - Visit 4: 15 minutes.   Please note, participants completed assent and parental consent at home. This is not being included into the total active time commitment. |
| **Planned interim analyses** | The progress of the trial will be monitored as detailed in Data Safety and Monitoring Plan. An interim analysis will be performed to evaluate the reliability and validity of the study instrument, the questionnaire. |
| **Statistical analysis** | Data will be collected, entered into a database, and analyzed using Stata. The distribution of the data, and appropriate statistical measures will be calculated. The scores before and after the teaching sessions will be compared using paired-t-test. Multivariate regression analysis will be used to determine whether the independent variable is predictive of the outcome after adjustment for covariates. |
| **Rationale for Number of Subjects** | A sample size of 504 subjects (252 subjects in each group) will provide a power of 80% to detect a change in questionnaire score by t-test with a two-sided type I error of 0.05. Considering the drop-out rate, we proposed to recruit a total of 600 subjects (300 in each group). |

# INTRODUCTION

Air pollution continues to have proven negative impact on the health of children and adolescents. Air pollution is a major environmental problem with important health consequences including cancer and cardiopulmonary diseases that affects billions of people around the world. Multiple studies have shown air pollution in general and its individual components, such as ozone and particulate matter, to be associated with increased morbidity and mortality in humans. Despite the wealth of scientific literature on the health effects of air pollution, the public support for generation of policies and regulation of the sources of pollution has remained modest at best. One potential cause of this disconnect between the state of scientific knowledge and the public and political support for aggressive regulation for protection of environment may be the lack of awareness and understanding of the available knowledge. However, there has been substantial media attention to the ongoing environmental problems in the recent years, and despite this publicity, the public and political support for the necessary steps to battle air pollution remains low. Perhaps, an important impedance for the support is the established lifestyle demands of the current generation of adults. The current generations have grown with little understanding of environmental and air pollution, which may make substantial changes in their attitudes more difficult. Given above, an important way to affect the future personal choices and public support for necessary regulation and policies would be to provide adequate education to the children who will form the future generations of our society.

## Preliminary Studies

Multiple longitudinal studies have demonstrated the association between air pollution and reduced lung function (Lippmann et al., 2014, Dons et al., 2014, Fruin et al., 2014). A 2004 study from Gauderman and colleagues demonstrated the significant association between exposure to pollution in the form of NO2, acid vapor, elemental carbon, and particulate matter (PM2.5) and a reduction in forced expiratory volume in the first second (FEV1) (Gauderman et al., 2004). In particular, exposure to tropospheric ozone has been linked to an increase in bronchial hyperirritability in healthy individuals (as well as rhesus monkeys). Reducing exposure to pollution is of both a policy and public health importance. Focusing on public health, behavioral intervention is key for reducing individual exposure. Intervention has had success in positively impacting individual environmental behavior through various means, including an increase in curbside recycling (Schultz et al., 1999) and a reduction in the number of miles driven and trips taken during days of poor air quality (Henry et al., 2002).

# SIGNIFICANCE

Air pollution is a global public health issue affecting billions of people around the world. Air pollution is on the rise, and any intervention that could potentially improve air quality would be highly beneficial to the broader society. It is increasingly important to provide a method through which the public could be better educated about air pollution in a way that would positively impact their understanding and future behavior towards environmentally friendlier choices.

# STUDY RATIONALE

Air pollution is a major environmental problem with important health consequences including cancer, cardiovascular, and pulmonary diseases that affects billions of people around the world. Multiple studies have shown air pollution in general and its individual components, such as ozone and particulate matter, to be associated with increased morbidity and mortality in humans. Despite the wealth of scientific literature on the health effects of air pollution, the public’s personal choices in their daily lives continues to be largely detrimental towards the environment, and the public support for generation of policies to regulate sources of pollution has remained modest at best.

One potential cause of the disconnect between the state of scientific knowledge and the public and political support for aggressive regulation to protect the environment may be the lack of awareness and understanding of the available knowledge. However, there has been substantial media attention to the ongoing environmental problems in the recent years, and despite this publicity, the public and political support for the necessary steps to battle air pollution has remained low. An important impedance to the required support for environmental protection may be the established lifestyle demands of the current generations of adults. The current adult generations have mostly grown with little understanding of the human contribution to air pollution and their impact on the environment, making any substantial change to their behavior challenging.

A potential solution to this problem may be to focus on the future generations to see whether providing appropriate education may result in lifestyles that include beneficial behaviors towards the environment since their lifestyles and habits are as yet unformed and more amenable to influence. However, whether teaching the adolescents about the health effects of air pollution would affect their future understanding and awareness of air pollution or forms their future behavior to more environmentally sound life choices is unclear.

## Risk/Benefit Assessment

The risks of this study are minimal compared to potential benefits it holds for public health, both locally and globally. Air pollution is a significant and escalating problem affecting numerous countries. The findings of this study can inform the development of future interventions aimed at promoting environmental awareness and behavior change among adolescents and ultimately contribute to reduction of the global public health burden of air pollution.

# STUDY OBJECTIVES

## Primary Objective

The hypothesis of this study is that, educating adolescents about health effects of air pollution through a short interactive evidence-based teaching session will shape their behavior to make personal choices that are more environmentally friendly.

## Secondary Objectives

The secondary objective of the study is educating adolescents about health effects of air pollution through a short interactive evidence-based teaching session can improve their long-term understanding of human contribution to air pollution.

# STUDY DESIGN

## Overview

This is a double-blind randomized placebo-controlled clinical trial to examine the long-term efficacy of a short classroom-based teaching session about air pollution on the understanding and behavioral choices of middle school students, The study will be using a repeated measure design. A one-hour interactive script-based evidence-supported teaching curriculum about air pollution will be developed and its effects on climate change and human health.

Furthermore, to assess the effect of the teaching session, we developed a survey questionnaire with two topic domains to evaluate the understanding and future behavioral choices of the participating adolescents towards air pollution. We also developed a one-hour teaching session about health benefits of vaccination to be used as the control teaching session.

## Questionnaire

The questionnaire was developed to assess two domains: (1) adolescents’ understanding of air pollution, its sources, and its environmental and health effects and (2) adolescents’ future behavior based on their report of personal behavioral choices as well as their support for public policies with potentially important effects on air pollution, environment, and climate change (https://[name].ucsf.edu/questionnaires-powerpoints). It consisted of 15 questions which were divided into the two domains gauged towards quantification of adolescents’ understanding and behavioral choices.

The questionnaire is designed to generate two scores. The multiple-choice answers to each question were weighted to have a minimum score of 1 and a maximum score of 4 (Table 1). The understanding domain section contained 5 multiple-choice questions designed to target and quantify the understanding of the participants with a score ranging from a minimum of 5 to a maximum of 20 possible points. The behavior domain section contained 10 questions (7 multiple-choice and 3 free-narrative response) designed to target and quantify behavioral choices of participants with a score ranging from a minimum of 10 to a maximum of 38 possible points.

## Teaching session

The teaching sessions are one hour in duration, script-based, and associated with a PowerPoint slide presentation (https://[name].ucsf.edu/questionnaires-powerpoints). The intervention (air pollution) teaching session was developed by our research group based on the available scientific literature. The intervention session will also involve two activities:

- One will involve breathing through a straw to replicate the effect of breathing with lung inflammation.
- The second activity will be spirometry forcefully exhaling through an electronic spirometer to measure lung function.

# CRITERIA FOR EVALUATION

## Efficacy Endpoints

The study primary and secondary outcomes are listed below:

- The primary outcome of the study is the questionnaire behavioral domain score.
- The secondary outcomes are the questionnaire total and understanding domain score.

## Safety Evaluations

Not applicable.

# SUBJECT SELECTION

## Recruitment, Eligibility, and Study Population

Middle school students in the age range of 13 to 15 from two schools will be recruited from Piedmont Middle School and KIPP Heartwood Academy. Two to four weeks before the intervention is scheduled to take place, the participating teachers will be provided with a list of eligibility criteria, and will assess the eligibility of students, then provide the study personnel with a list of eligible students. These eligible students will be given the Information Letter and the Consent/Assent form to take home and complete. Those who complete the form and provide assent to participate in the study will be enrolled, and their eligibility will be further verified by study personnel through the demographic questionnaire.

## Vulnerable population

It is appropriate to include children in this study because the main purpose of this study is to focus on the efficacy of school-based intervention in changing the behavior of middle-school adolescents, and it is therefore essential to include children in this research so that the study population can properly reflect the target population.

## Guardian/ parental consent

The prospective student’s parents or guardians will receive information regarding their child’s invitation to participate in the study. They will be provided with a detailed description of the research study, including its nature and purpose, and asked to provide consent for their child’s participation. Only participants who have provided both assent and parental or guardian consent will be enrolled in the study, ensuring that participation is voluntary and contingent upon appropriate authorization.

## Inclusion Criteria

1. 13-15 years of age.
2. Middle school student.
3. Ability to read, understand, and write in English (at the middle-school level).
4. Willingness to participate in follow-up visits of the study.

## Exclusion criteria

1. Learning disabilities (such as autism).
2. Moving out of the area within the next 6 months
3. Inability to complete pre-intervention questionnaire.

# RANDOMIZATION

In this randomized control trial, eligible students will be randomized by block randomization, as explained below. The students will be assigned a study ID number through sorting their last names (and first names if necessary) alphabetically and then assigned a study ID number. They will then be partitioned by simple randomization of their subject ID number within their classrooms using STATA software to either receive a one-hour script-based teaching on either the effects of air pollution on lung health (intervention group) or the role of vaccination in public health (control group), such that about equal numbers of students in each classroom were assigned to intervention and control groups.

# BLINDING

In this study, blinding of participants and study staff to the intervention will not be feasible. However, to minimize bias, the data from the questionnaires will be entered into a database by two research assistants who will also be blinded to the assignment of the participants. Furthermore, the scoring of the free-narrative survey responses will be carried out by two observers who will be blinded to the participant assignment. These observers will adhere to the pre-defined guidelines that categorizes response from no response or an irrelevant response to a relevant response or a response related to a recent relevant event. This blinding procedure will ensure that the scoring of free-narrative responses and the data entry into the databases are conducted objectively and without knowledge of the participant assignment.

# STUDY PROCEDURES AND GUIDELINES

Prior to conducting any study-related activities, written informed consent and the Health Insurance Portability and Accountability Act (HIPAA) authorization will be signed by the parent or guardian and we will also get an assent from the participant.

## Clinical Assessments

### Demographics

Demographic information (date of birth, gender, race, family income) will be recorded at Visit 1.

### Clinical Laboratory Measurements

Not applicable

## Evaluations by visit

Participants will be asked to complete a total of three in-person visits and one at-home over a period of at least 12 months.

Acquisition of Informed Consent: Parents/guardians of students who meet the eligibility criteria will be sent a set of papers containing:

- A letter explaining the purpose and methods of the study, and
- A letter of consent and assent for both the parent and student to sign.

All documents will be written in simple English and Spanish (<8th grade level). These forms will be brought to school, and those students with completed consent/assent forms will be eligible to participate in the study.

To ensure understanding of the consent and assent material, study staff will review the consent document over the phone with the potential subjects/ guardian.

**Visit 1**

- Questionnaire: The enrolled students will complete a survey (15 multiple-choice questions; five targeting understanding (score range 5-20); ten targeting behavioral choices (score range 10-38)) designed to evaluate their understanding and predict their future behavior towards air pollution immediately before the intervention.
- Teaching session: participants will be given a one-hour script-based teaching on either the effects of air pollution on lung health (intervention group) or the role of vaccination in public health (control group). The teaching session also includes offering students to breathe through a straw and also undergo spirometry.
- Questionnaire: The enrolled students will complete the same survey immediately after the intervention.

**Visit 2**

- Questionnaire: The enrolled students will complete the same survey in about three months after the intervention.

**Visit 3**

- Questionnaire: The enrolled students will complete the same survey in about six months after the intervention

**Visit 4**

- Questionnaire: The enrolled students will complete the same survey in about twelve months after the intervention

Due to scholastic schedules and holidays the questionnaires may be applied within 8 weeks of the planned schedule (for example 1 to 5 months or 4 to 8 months or 10 to 14 months).

# STATISTICAL METHODS AND CONSIDERATIONS

Data will be collected, entered into a database, and analyzed using statistical software. The distribution of the data, and the appropriate statistical measures will be calculated. The questionnaire scores before and after the teaching sessions will be compared using paired-t-test. In addition, multivariable regression analysis will be performed to determine whether or not the independent variable is predictive of the outcome and to determine the contribution of covariates.

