## Sample size

For sample size and power calculation, we made the following assumptions:

- Minimally important difference in questionnaire score of 10% change due to the intervention.
- Standard deviation of change in score of 40%.
- A drop-out rate of about 20% due to factoring including movement of subjects out of the area.

A sample size of 504 subjects (252 subjects in each group) will provide a power of 80% to detect a change in questionnaire score by t-test with a two-sided type I error of 0.05. Considering the drop-out rate, we proposed to recruit a total of 600 subjects (300 in each group).

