## Statistical Models

- Paired t-test comparison of pre versus post teaching session.
- Linear regression modeling analysis will be performed to compare the scores and change in them between the intervention and control group with adjustment for covariates including age, sex, race, ethnicity, income level, and assigned classrooms as appropriate.
- Multivariate generalized estimating equation regression analysis will be performed to determine whether there is an incremental effect from “time” on scores and change in scores with adjustment for covariates including age, sex, race, ethnicity, income level, and assigned classrooms as appropriate.

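### A within-group pre/post paired t-test is listed first throughout, and the planned between-arm comparison of the behavior score is never made the deciding test

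*Protocol*

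**What the plan says.** Three places in the protocol describe the analysis, and each starts with the paired test.

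- Synopsis, Statistical analysis: "The scores before and after the teaching sessions will be compared using paired-t-test". A regression on the independent variable, adjusted for covariates, follows.
- Section 13: "The questionnaire scores before and after the teaching sessions will be compared using paired-t-test". The next sentence adds, as a further step, that "multivariable regression analysis will be performed to determine whether or not the independent variable is predictive of the outcome". Section 13.2.1 defines the independent variable as the air-pollution session.
- Section 13.4: the first bullet is "Paired t-test comparison of pre versus post teaching session". The second bullet is the between-arm analysis: "Linear regression modeling analysis will be performed to compare the scores and change in them between the intervention and control group with adjustment for covariates". The third is a longitudinal model: "Multivariate generalized estimating equation regression analysis will be performed to determine whether there is an incremental effect from “time” on scores and change in scores". No arm-by-time term is named.

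Section 8.1 defines the endpoint: "The primary outcome of the study is the questionnaire behavioral domain score". It gives neither a time point nor a contrast between arms. No analysis is labelled primary or confirmatory anywhere in the protocol.

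Section 13.1 states "A sample size of 504 subjects (252 subjects in each group) will provide a power of 80" percent, by a t-test that it does not identify as paired or two-sample. The paired test is the only t-test named elsewhere.

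**The concern.** The objective is causal: does air-pollution teaching shift behavioral choices? The vaccination session was built as the control for that question. A pre/post test within a group uses no control data. The same survey is given before teaching, immediately afterwards, and at about 3, 6 and 12 months (Section 12.2). Familiarity with the questions, outside events and, at the later visits, maturation can therefore move scores in both arms without any effect of the air-pollution session.

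The protocol does not say which result settles the primary outcome. A significant pre/post change in the intervention arm could thus be reported as efficacy, consistently with the text, even if the control arm moved by the same amount. Running the paired test in each arm does not solve this, because significance in one arm and not in the other is not a test of the difference between arms.

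**Working it through.** **1. Which test does the stated sample size belong to?**

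Inputs from Section 13.1: important difference 10%, standard deviation of change 40%, two-sided type I error 0.05, power 80%. The standardised difference is 10/40 = 0.25. The normal quantiles are 1.960 and 0.842.

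- Two-sample comparison of change: n per group = 2 × ((1.960 + 0.842) × 40/10)² ≈ 251.2, rounded up to 252, or 504 in total. This reproduces the stated figure. Power at 252 per group is 80.1% by the normal approximation and 80.0% by the noncentral t.
- Paired test in one group: n = ((1.960 + 0.842) × 40/10)² ≈ 125.6, so 126 by the normal approximation; the t distribution gives 127.5, so 128. With 252 students the paired test would have 97.7% power.

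Only the two-sample comparison of change returns 252 per group.

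**2. What can the paired test do when teaching has no effect?**

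Inputs: standard deviation of change 40% (Section 13.1); 240 analysed per arm, from 300 recruited less 20% drop-out (300 × 0.80). The drift common to both arms is an assumption, since the protocol gives no figure for it. Values of 4%, 6% and 8% are used (0.10, 0.15 and 0.20 standard deviations of change), all below the plan's 10% important difference.

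The standard error of the mean change in one arm is 40/√240 = 2.58. The noncentrality is drift/2.58. The rejection probability is that of a two-sided t-test on 239 degrees of freedom.

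| Assumed common drift | Noncentrality | Paired test significant, no teaching effect | Exactly one arm significant |
|---|---|---|---|
| 4% | 1.55 | 34% | 45% |
| 6% | 2.32 | 64% | 46% |
| 8% | 3.10 | 87% | 23% |

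The last column is 2p(1 − p), with p the unrounded rejection probability and the arms independent; for 4% drift, 2 × 0.339 × 0.661 = 0.448. With no drift the paired test rejects 5% of the time, as it should.

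**3. The between-arm comparison under the same drift.**

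The expected contrast is (teaching effect + drift) − drift = teaching effect. Common drift cancels, and with no teaching effect the type I error stays at 5% whatever the drift.

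**The case against.** The strongest reply is that the valid analysis is already planned. Section 13.4 compares scores and change between intervention and control with covariate adjustment, and the regressions in the synopsis and Section 13 test the teaching session as predictor. The sample size fits only that comparison, and the first sizing assumption refers to change caused by the intervention. On this view the between-arm test was intended all along and the paired tests are a conventional descriptive opening, possibly run in both arms, since the text speaks of sessions in the plural. If the paired test covers only the same-day surveys, maturation over a year is irrelevant to it, though retest effects are not. The choice of confirmatory model could also be left to a statistical analysis plan that is not shown.

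Much of this stands. A reader might infer from the order of listing that the paired test is the headline efficacy analysis and that the trial ignores its randomised control. The documents do not support that: no analysis carries such a label, and Section 13.4 uses the control arm. The sample size is evidence for the between-arm test rather than against the plan.

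The reply does not remove the point. The protocol does more than leave detail open. It states, first in all three places, a test that cannot answer the objective, gives it no subordinate role, and presents regression in Section 13 as an addition. Section 13.1 then refers to a t-test when the only one named elsewhere is not the one the trial was sized for.

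**Conclusion.** The point holds in a limited form. The protocol puts a within-group pre/post test first in every description of the analysis and does not make the planned between-arm regression the deciding test of the behavior domain score, although its own sample size is that of a two-sample comparison of change. The sample-size result uses only the protocol's inputs.

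The rejection rates of 34%, 64% and 87% depend on the assumed drift and on 240 analysed per arm. They show what could happen if a paired result were reported as efficacy; they do not estimate the trial's actual error rate and say nothing about the between-arm regression, which is protected against common drift. The correction still matters, because it determines whether the primary claim rests on randomisation.

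**What to change.** - In Sections 2, 13 and 13.4, name one primary analysis of the behavior domain score: the between-arm difference, intervention minus control, from a linear regression adjusted for the baseline score, at one stated time point.
- In the same places, label the paired t-tests as descriptive within-arm summaries that support no efficacy claim.
- In Section 13.1, state that the t-test used for sizing is the two-sample comparison of change between arms.

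The cost is wording only. The regression is already planned, the baseline score is already collected at Visit 1, and the 504 evaluable subjects (252 per group) already fit the between-arm comparison.
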